### 11.4.3 Secondary Analyses

Secondary analyses will be exploratory in nature and aim to measure the ITT effect. All estimates will be presented with 95% confidence intervals.

The key secondary outcome a (Symptomatic UTI (based on clinical diagnosis supported by measured bacteriuria of ≥10^5^ cfu/ml) treated with antibiotics*)* will be analysed as described for the primary endpoint (Section 11.4.2). Results (size and direction of the effect) will be compared informally to the primary endpoint.

Secondary outcomes *b – m* (see Section 5.2) will be analysed with *generalised linear mixed models (GLMM) with binomial error distribution*, including trial arm as predictor and study centre as random effect. Estimates will be reported as odds ratios (OR).

Secondary outcomes *n – p* (see Section 5.2) will be treated as count data and analysed with *GLMM with poisson error distribution*, including trial arm as predictor and study centre as random effect. Estimates will be reported as relative effects.

Secondary outcomes *r – s* (see Section 5.2) will be analysed by means of linear mixed models (LMM), including trial arm as predictor and study centre as random effect. Estimates will be reported as absolute effects.

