## Secondary Outcomes

1. Symptomatic UTI (based on clinical diagnosis and judgement of the treating physician supported by measured bacteriuria of ≥10^5^ cfu/ml) treated with antimicrobial agents (**key secondary outcome**)
2. Symptomatic cystitis (based on clinical diagnosis)
3. Symptomatic epididymitis (based on clinical diagnosis)
4. Symptomatic pyelonephritis (based on clinical diagnosis)
5. Symptomatic prostatitis (based on clinical diagnosis)
6. Symptomatic urethritis (based on clinical diagnosis)
7. Urosepsis (based on clinical diagnosis)
8. Prescription of antibiotics (for any reason)
9. Asymptomatic bacteriuria of ≥10^5^ cfu/ml treated with antimicrobial agents
10. Detection of multidrug-resistant bacteria in urine culture (3MRGN, 4MRGN)
11. Any *Clostridium difficile*-associated infection
12. Re-hospitalisation (within 30 days after randomisation)
13. All-cause mortality
14. Duration of catheterisation (cumulative sum of days between randomisation and end of catheterisation or day 30)
15. Duration of hospital stay (cumulative sum of hospital days between randomisation and day 30)
16. Duration of intensive care unit stay (cumulative sum of ICU days between randomisation and day 30)
17. Prescribed defined daily doses (DDD) of antibiotics (cumulative sum of DDD from randomisation to day 30)
18. Change of International Prostate Symptom Score (prior to surgery and at day 30 after randomisation)
19. Change of Quality of life Score (prior to surgery and at day 30 after randomisation)

All sensitivity and subgroup analyses will be done for the primary outcome and for the key secondary outcome (see Section 11).

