# STUDY DESIGN

## General study design and justification of design

This is a randomised controlled, non-inferiority, parallel group, double-blinded trial with a 1:1 randomisation ratio in five urological departments in Switzerland. Study participations are either randomised to a guideline-conform single-dose AP (Group A) or to a 3-day AP (Group B). Physicians, patients and outcome assessors will be blinded. The trial is based on routinely collected data during TURP and GL of the prostate until day 30 after surgery (i.e. randomisation).

Only a randomised controlled trial would be able to provide reliable evidence to guide decision-making in this setting. Non-randomised observational methods would carry a high risk of bias and not allow to make causal inferences about the comparative merits of both treatment strategies.

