**Prescribed defined daily doses (DDD) of antibiotics (cumulative sum of DDD from randomisation to day 30)**

From each prescribed antibiotic (assessment same as for primary outcome; see section “9.2.1 Assessment of primary outcome”) the following information will be recorded: Specific compound which, dose in mg per intake, how many intakes per day, and for how many days the antibiotic was prescribed. Based on this information the defined daily doses according to the ATC system (33) will be calculated. If a patient states that the prescribed antibiotics were not taken, these will anyway be counted under “prescribed DDD”.

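### The Poisson models for catheter, hospital and ICU days give valid 95% intervals only if variance equals the mean, which the protocol neither supports nor checks; the DDD outcome (letter q) has no model

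*Protocol*

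**What the plan says.** Section 11.4.3 of the protocol assigns a method to each lettered group of secondary outcomes in section 5.2. Outcome a is analysed like the primary outcome, b to m by a binomial mixed model, and r to s by a linear mixed model. Outcomes n to p "will be treated as count data and analysed with" a "GLMM with poisson error distribution", "including trial arm as predictor and study centre as random effect". The same section promises 95% confidence intervals for all estimates and calls the secondary analyses exploratory. It names no dispersion parameter, patient-level random effect or robust variance.

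Section 5.2 lists 19 outcomes. Items 14 to 16 are catheter, hospital and ICU days. For example, item 14 is "Duration of catheterisation (cumulative sum of days between randomisation and end of catheterisation or day 30" and item 16 is "Duration of intensive care unit stay (cumulative sum of ICU days between randomisation and day 30". Item 17 is "Prescribed defined daily doses (DDD) of antibiotics (cumulative sum of DDD from randomisation to day 30". Items 18 and 19 are the changes in the prostate symptom and quality of life scores.

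**The concern.** These outcomes are sums of days over a 30-day window, not counts of independent events. A Poisson model ties the variance to the mean. A centre random effect relaxes that only for differences between centres, of which there are few: "1:1 randomisation ratio in five urological departments in Switzerland". Patient-to-patient variation within a centre stays fixed at the Poisson value.

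If the true variation is larger, the intervals are too narrow and chance differences in hospital or ICU days may be read as real. If it is smaller, the intervals are too wide and a real difference may be missed. These are outcomes in which readers will look for harm from shorter prophylaxis.

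The gap at letter q matters because section 11.2 justifies the margin partly by the reduction in antibiotic use. DDD is the only secondary outcome that measures the amount of antibiotic prescribed; outcome h records only whether any was prescribed.

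**Working it through.** **Inputs from the protocol.** The model is as described above. There are 1,416 evaluable patients, so 708 per arm (section 11.2). The protocol states no figure for outcomes n to p. Its sample size for the primary test does reproduce: with 9% in both arms, a margin of 4.4% and the continuity-corrected Wilson-type interval, simulated power at 1,416 is 80.3%, and 1,416/0.9 rounds up to 1,574. Nothing below touches that.

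**Letters.** Counting the items of section 5.2 gives n = 14 (catheter days), o = 15 (hospital days), p = 16 (ICU days), q = 17 (DDD), r = 18 and s = 19 (the two scores). The labels a, b–f and g in the table of section 9.1 fit this count. So does section 11.5, which singles out r and s. Section 11.4.3 goes from n–p to r–s, so q is skipped.

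**Which way might the dispersion go?** The protocol points both ways.
- Section 9.2.2 adds later catheters, re-hospitalisations and further ICU stays to the totals, and section 10.1.1 calls prolonged hospitalisation common. Both suggest a variance above the mean.
- Section 3.1 puts catheter removal in general on the day before day 3, and section 9.1 labels day 3 as discharge. Both suggest tight clustering in routine cases, hence a variance below the mean.

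**Effect on the interval.** Let φ be the true within-centre variance divided by the mean. The true standard error of the log mean ratio is √φ times the one the model reports. Coverage of the nominal 95% interval is therefore 2Φ(1.96/√φ) − 1, and its width is 1/√φ of the correct width. All values of φ are assumptions.

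| φ | Coverage | Width relative to correct |
|---|---|---|
| 0.25 | about 100% | 2.0 |
| 0.5 | 99.4% | 1.41 |
| 1 | 95.0% | 1.0 |
| 1.5 | 89.0% | 0.82 |
| 2 | 83.4% | 0.71 |
| 3 | 74.2% | 0.58 |
| 5 | 61.9% | 0.45 |

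For φ = 2, for instance, 1.96/√2 = 1.386 and 2Φ(1.386) − 1 = 0.834.

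**Rare ICU stays.** Assume 1% of men have a stay, with geometric length of mean m days. Then the mean is 0.01m, the second moment is 0.01(2m² − m), and φ = 2m − 1 − 0.01m.
- One-day stays (m = 1): φ = 0.99, false-positive rate about 5%.
- m = 1.5: φ = 1.985, about 16%.
- m = 3: φ = 4.97, about 38%. Simulation at 708 per arm gave about 37%.

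**Does a correction work?** Four assumed scenarios were simulated with no true difference, 1,416 patients and 1,500 trials each. Centre entered as fixed effects in place of the random effect; the ICU scenario had no centre term and assumed stays in 2% of men.

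| Assumed scenario | φ | Poisson coverage | Dispersion-corrected coverage |
|---|---|---|---|
| Tightly clustered stay | 0.24 | about 100% | 94.6% |
| Over-dispersed stay | 2.0 | 82.8% | 95.1% |
| Rare ICU days | 3.6 | 70.7% | 95.7% |
| Catheter days with some re-catheterisation | 4.4 | 65.8% | 94.3% |

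In the separate ICU scenario with 1% of men and mean 3 days, robust standard errors brought the false-positive rate from about 37% to about 7%. That is far better, but not exact with so few stays.

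**The case against.** The strongest reply is that the protocol gives no dispersion, so every coverage figure rests on an assumption, and the assumptions run both ways. That stands. A reader might infer that the intervals will certainly be wrong; the document does not support that. It supports only that they are right in one special case, for which the protocol gives no reason.

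Second, these analyses are exploratory, and the Poisson mean ratio remains a usable estimate when the variance is misspecified. Both are true and limit the consequence. They do not rescue an interval labelled 95%.

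Third, dispersion checks are often left to an analysis plan, and section 11.4.6 mentions a detailed one. This carries some weight. But the protocol does not leave the matter open: it fixes the error distribution and the terms of the model. Likewise, q is the only secondary outcome of the 19 left without a method.

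Two stronger readings of the DDD outcome should be set aside. A reader might infer from section 9.2.2 that only antibiotics found through the UTI assessment count. The paragraph there on antibiotic prescription says that all prescriptions count, whether or not a symptomatic UTI occurred. The sentence "If a patient states that the prescribed antibiotics were not taken, these will anyway be counted" deals with non-intake and does not settle the status of study tablets. A reader might also infer that DDD will show an effect of the wrong sign. That is not shown. Five active tablets against none is a difference fixed by design, and DDD without study medication is a legitimate outcome in its own right. What remains is that the protocol does not say which of the two is meant.

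**Conclusion.** The point holds in a limited form. As fixed in section 11.4.3, the intervals for catheter, hospital and ICU days are valid only if within-centre variance equals the mean. Summed multi-day stays make that equality doubtful, and nothing in the protocol supports or tests it. Under an assumed ratio of 0.25 to 5, coverage ranges from about 100% to 62%. For ICU days with stays in an assumed 1% of men, the false-positive rate ranges from about 5% to 38%, depending on length of stay. The actual size is unknown until the dispersion is seen.

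The omission of q is a plain gap between sections 5.2 and 11.4.3 and rests on no assumption. The status of the study tablets in the DDD sum is a matter to clarify, not a demonstrated bias.

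Both parts concern exploratory outcomes. The primary non-inferiority conclusion, the key secondary outcome and the sample size are unaffected. The change is worth making because it costs almost nothing.

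**What to change.** - For n to p, keep the ratio (or difference) of means as the effect measure, but base the 95% interval on sandwich standard errors, a quasi-Poisson dispersion estimate or a bootstrap.
- Report ICU stay also as the proportion of men with any stay in each arm, since few stays make even a robust interval for mean days approximate.
- Reconcile section 5.2 with section 11.4.3 by extending the same dispersion-robust comparison of means to q. DDD is a non-integer sum, so a plain Poisson likelihood does not fit it.
- State in section 9.2.2 whether the blinded study tablets count towards DDD, and preferably report DDD both with and without study medication.

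The cost is a few sentences of protocol or analysis-plan wording and a different model call, settled before unblinding. No new data are needed: drug, dose and duration of each prescribed antibiotic are already recorded, and study tablets follow from allocation.

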**Change of International Prostate Symptom Score (prior to randomisation and at day 30 after randomisation)**

Prior to the surgery and at the routine control at day 30, patients are routinely handed out the validated International Prostate Symptom Score (36) consisting of 7 questions. Each question concerning urinary symptoms allows the patient to choose one out of six answers indicating increasing severity of the particular symptom. The answers are assigned points from 0 to 5. The total score can therefore range from 0 to 35 (asymptomatic to very symptomatic). The change of the score is calculated by subtracting the score at day 30 from the score at enrolment.

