## Procedures at each visit

### See also Section 9.1.

### 9.3.1 Enrolment

For each patient at enrolment (approximately 7 days before surgery): eligibility screen, informed consent and assessment of baseline variables (study site, study ID, BMI, ASA score, blood counts, anticoagulation, PSA, prostate volume, post voiding residual volume, catheterisation, International Prostate Symptom Score/Quality of Life score, history of urinary tract infections) is performed.

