The sample size was calculated using a re-sampling procedure. Each sample size, n_i_=1,...,111 = 800, ..., 3000, was evaluated by simulating 999 individual samples of n_i_ patients based on the assumptions described above. The difference in the observed event rates p_idAP_ – p_3dAP_ was compared with the non-inferiority margin δ, using a two-sided 95 % confidence interval, calculated using a continuity-corrected modification of Wilson’s score method (41). Non-inferiority was declared if the upper limit of this 95 % confidence interval was no larger than the non-inferiority margin δ. Figure 2 shows the relationship between the total sample size (number of patients, not including drop-outs) and the expected absolute difference in the UTI rate between the two trial arms. For an assumed event rate of 9% in both trial arms, and a δ of 4.4%, a total of 1574 patients should be recruited, in order to have 1416 evaluable patients.

[figure not shown]
**Figure 2:** Total sample size needed to show possible non-inferiority of single-dose AP to 3-day AP, depending on the absolute difference in the UTI rate. An examples is shown for an absolute difference of 0% and a power of 80%. The curves are smoothed and for illustration only.

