## Handling of missing data and drop-outs

Drop-outs will not be replaced. The number of drop-outs will be reported for each trial arm separately, indicating the reason for drop-out.

**Primary analysis:** For the ITT analysis, missing values will be imputed using multiple imputation methods. As sensitivity analysis, the analysis will be repeated using inverse probability censored weighting (IPCW) methodology (43). This approach accounts for missingness based on a logistic regression model for the probability of having a complete follow-up given past history covariates and outcomes. By using inverse weights, the impact of underrepresented subjects is inflated, so that one can observe associations that would have been observed if all subjects had stayed in the study, assuming the model is correctly specified. For the PP analysis, a complete case approach is applied where no missing values are possible.

**Secondary analyses:** Secondary analyses will be performed primarily as complete case analyses. For the key secondary endpoint [a] and secondary endpoints [r] and [s], additional (sensitivity) analyses will be performed, as described for the primary endpoint. For all other secondary endpoints, missing data will only be imputed or IPCW applied if the amount of missing values is considerable (i.e. more than 5% of values missing in one treatment group, more missing values than events in one group). This means that the number of patients may vary among analyses.

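### IPSS and quality-of-life change are modelled without the enrolment score as a covariate, although it is collected; adjusting would usually tighten the estimates, by an amount the protocol cannot fix (minor)

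*Protocol*

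**What the plan says.** Outcomes r and s are the last two entries in the list in Section 5.2. Outcome r is "Change of International Prostate Symptom Score (prior to surgery and at day 30 after randomisation"), and s is the matching quality-of-life item. Section 9.2.2 makes both of them raw differences: "The change of the score is calculated by subtracting the score at day 30 from the score at enrolment".

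Section 11.4.3 names the model: these outcomes "will be analysed by means of linear mixed models (LMM), including trial arm as predictor and study centre as random effect". Neither the enrolment score nor surgery type is listed.

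The enrolment score is available. The list of baseline variables in Section 9.3.1 ends with "International Prostate Symptom Score/Quality of Life score, history of urinary tract infections) is performed", and the table in Section 9.1 marks both scores at enrolment and at day 30.

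On status, Section 11.4.3 says "Secondary analyses will be exploratory in nature and aim to measure the ITT effect". On missing data, Section 11.5 starts from complete cases and then says "For the key secondary endpoint [a] and secondary endpoints [r] and [s], additional (sensitivity) analyses will be performed, as described for the primary endpoint". Those extra analyses (multiple imputation and inverse probability weighting) deal with missing values. They do not put the enrolment score into the outcome model.

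**The concern.** Subtracting the enrolment score is not the same as adjusting for it. Subtraction fixes the coefficient of baseline at 1, whereas a covariate lets the data estimate it. If the true coefficient is below 1, subtraction brings in baseline variation that says nothing about treatment. The estimate is then noisier, and part of any chance baseline difference between the arms stays in it. The scale itself ties change to baseline: "The total score can therefore range from 0 to 35 (asymptomatic to very symptomatic"), so a man with a low enrolment score has little room to improve.

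What is at stake is the width of two confidence intervals. For exploratory outcomes without a test or margin, the estimate and its interval are the whole result.

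In addition, Section 6.2.1 minimises on centre and surgery type, while the model for r and s carries only centre.

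**Working it through.** **Inputs.** The protocol states no sample size, SD, correlation or power for IPSS or quality of life, so there is no figure of its own to reproduce on this point. For scale I use the primary-outcome numbers in Section 11.2: "a total of 1574 patients should be recruited, in order to have 1416 evaluable patients". They are consistent with each other: 1,416 / 0.9 = 1,573.3, rounded up to 1,574. A simulation with the continuity-corrected Wilson interval gives 80.2% power at 1,416. This yields 1,416 / 2 = 708 per arm. The correlation rho and the ratio k = s1/s0 (day-30 SD over enrolment SD) are assumptions, varied over 0.1 to 0.8 and 0.6 to 1.25. SDs and correlation are to be read as within centre.

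**Direction.** The variance of the arm difference is proportional to

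- raw change: s0² + s1² − 2·rho·s0·s1
- adjusted for baseline: s1²·(1 − rho²)

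The first minus the second is s0² − 2·rho·s0·s1 + rho²·s1² = (s0 − rho·s1)². This is never negative, and it is zero only when rho·s1 = s0.

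**Size with equal SDs.** The ratio adjusted/change is (1 − rho²) / [2(1 − rho)] = (1 + rho)/2, so the saving is (1 − rho)/2. Standard errors in SD units with 708 per arm are √[2(1 − rho)]·√(2/708) for change and √(1 − rho²)·√(2/708) with adjustment, where √(2/708) = 0.053.

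| rho | variance saved | SE, change | SE, adjusted |
|---|---|---|---|
| 0.1 | 45% | 0.071 | 0.053 |
| 0.2 | 40% | 0.067 | 0.052 |
| 1/3 | 33% | 0.061 | 0.050 |
| 0.5 | 25% | 0.053 | 0.046 |
| 0.7 | 15% | 0.041 | 0.038 |
| 0.8 | 10% | 0.034 | 0.032 |

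**Size with unequal SDs.** The saving is 1 − k²(1 − rho²) / (1 + k² − 2·rho·k). Over rho 0.1 to 0.8:

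- k = 0.6: 64 to 71%
- k = 0.8: 36 to 57%
- k = 1.25: 33% at rho 0.1, falling to 0 at rho 0.8 (where rho·k = 1)

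**Chance imbalance.** The baseline difference between arms has standard error 0.053 SD, so its 95% range is ±1.96 × 0.053 = about ±0.10 SD. The change score passes on the fraction 1 − rho·k of it, which is 1 − rho with equal SDs. Written as day 30 minus enrolment, the sign is reversed. In the protocol's direction (enrolment minus day 30), the arm that starts worse appears to improve more. At rho 0.5 with equal SDs the carry-over is at most about 0.5 × 0.10 = 0.05 SD.

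**In scale points.** At rho 1/3 with equal SDs the 95% half-widths are 1.96 × 0.0614 = 0.120 SD and 1.96 × 0.0501 = 0.098 SD, a difference of 0.022 SD. The SD on a 0–35 scale cannot exceed 17.5, so this is at most 0.022 × 17.5 = about 0.4 IPSS points. On the 0–6 quality-of-life scale (SD at most 3) it is at most 0.07 points.

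**The case against.** The best defence is that nothing hangs on this. No hypothesis, margin or decision rule attaches to r or s. The planned estimator is unbiased over randomisations, and with about 708 per arm both intervals are already narrow. All of that stands and keeps the priority low. Fewer completed questionnaires would widen both intervals, but the variance ratio would not change at the same rho and SD ratio.

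A second defence is that covariates belong in the analysis plan. Section 11.4.6 refers to a detailed plan that is not at hand, and the word including need not be exhaustive. This stands only in part. The sentence sets out the model terms, names centre and omits baseline, so a plan that follows it would repeat the omission.

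Some readers might infer more than the documents support:

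- **That a third or more of the information is lost.** With equal SDs this needs rho of 1/3 or less. A low correlation after surgery is plausible, but the protocol does not document it.
- **That adjustment gains at every rho below 1.** This holds with equal SDs. In general the gain vanishes when rho·s1 = s0.
- **That the estimate is biased, or takes in the whole baseline difference.** With equal SDs a fraction (1 − rho) remains, as conditional error.
- **That centre is also missing.** It is already in the model as a random effect.

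**Conclusion.** The point holds as a minor improvement in efficiency. The protocol states a model for r and s that leaves out a baseline score it collects, and no other section puts that score in. Under a linear relation with a common slope, adjustment cannot increase the variance of the arm difference and usually reduces it. With equal SDs the reduction is 10% to 45% for rho from 0.8 to 0.1. Across SD ratios of 0.6 to 1.25 it runs from 0 to 71%. These ranges rest on assumed correlations and SDs, and the documents cannot narrow them. The remaining chance imbalance is small at the planned size. The primary non-inferiority conclusion and the sample size are untouched.

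**What to change.** In Section 11.4.3, add the enrolment score (IPSS for r, quality of life for s) as a covariate in the linear mixed model. Keep trial arm and the centre random effect. Add surgery type, because Section 6.2.1 uses it as a minimisation factor. The arm effect is the same whether the response is the day-30 score or the change, apart from the sign convention, once the enrolment score is in the model, so the outcome definitions in Sections 5.2 and 9.2.2 can stay.

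The cost is one phrase in the protocol or analysis plan. No new data or visits are needed. Making the change before unblinding also avoids a later, data-driven choice between adjusted and unadjusted estimates.
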